## Abstract

**Background:**

There remains no effective intervention capable of reversing most cases of dementia. Current research is focused on prevention by addressing risk factors that are shared between cardiovascular disease and dementia (e.g., hypertension) before the cognitive, functional, and behavioural symptoms of dementia manifest. A promising preventive treatment is exercise. This study describes the methods of a randomized controlled trial (RCT) that assesses the effects of aerobic exercise and behavioural support interventions in older adults at increased risk of dementia due to genetic and/or cardiovascular risk factors. The specific aims are to determine the effect of aerobic exercise on cognitive performance, explore the biological mechanisms that influence cognitive performance after exercise training, and determine if changes in cerebrovascular physiology and function persist 1 year after a 6-month aerobic exercise intervention followed by a 1-year behavioural support programme (at 18 months).

**Methods:**

We will recruit 264 participants (aged 50–80 years) at elevated risk of dementia. Participants will be randomly allocated into one of four treatment arms: (1) aerobic exercise and health behaviour support, (2) aerobic exercise and no health behaviour support, (3) stretching-toning and health behaviour support, and (4) stretching-toning and no health behaviour support. The aerobic exercise intervention will consist of three supervised walking/jogging sessions per week for 6 months, whereas the stretching-toning control intervention will consist of three supervised stretching-toning sessions per week also for 6 months. Following the exercise interventions, participants will receive either 1 year of ongoing telephone behavioural support or no telephone support. The primary aim is to determine the independent effect of aerobic exercise on a cognitive composite score in participants allocated to this intervention compared to participants allocated to the stretching-toning group. The secondary aims are to examine the effects of aerobic exercise on a number of secondary outcomes and determine whether aerobic exercise-related changes persist after a 1-year behavioural support programme (at 18 months).

**Discussion:**

This study will address knowledge gaps regarding the underlying mechanisms of the pro-cognitive effects of exercise by examining the potential mediating factors, including cerebrovascular/physiological, neuroimaging, sleep, and genetic factors that will provide novel biologic evidence on how aerobic exercise can prevent declines in cognition with ageing.

**Trial registration:**

ClinicalTrials.gov NCT03035851. Registered on 30 January 2017

## Background

Life expectancy is projected to rise over the coming decades for most industrialized countries [1]. There are already more than 1 billion people worldwide aged 60 years or older [2]. Despite the increase in longevity, the number of years spent in good physical health (e.g,. no mobility, functional, and/or cognitive impairments) has remained unchanged over the past few years in Canada [3]. There are a growing number of older individuals with age-related normative cognitive decline as well as Alzheimer’s disease and related dementias (ADRD). Recent estimates suggest that worldwide, ~ 50 million people currently have dementia, and by 2030, this is predicted to increase to ~ 82 million [4]. In Canada, ~ 500,000 older adults are now living with dementia [5]. Almost 40% of Canadians over the age of 65 have some degree of cognitive impairment [5]. Their direct cost care was estimated to be $10.4 billion CDN dollars in 2019 and are projected to climb to $16.6 billion CDN by 2031 [5]. The personal costs of dementia and these alarming public health estimates are motivating efforts to identify lifestyle interventions that can slow the progression of ADRD. In addition to focusing on treatment, studies have been targeting the prevention of neurodegenerative diseases with the aim of mitigating, delaying, or preventing the onset of ADRD [6–10].

Exercise is a promising method to reduce the risk of dementia in both healthy older adults and those at elevated risk of ADRD due to cardiovascular risk factors [11]. The physiological benefits of exercise in older adults are clear in the research literature and include improved arterial compliance (i.e., the ability of a vessel to expand as needed), endothelial function, energy metabolism, sleep quality, and muscle mass/strength [12]. Exercise also promotes cardiovascular fitness by improving global vascular health, including increases in middle cerebral artery vasodilation responses and cerebral blood flow (CBF) [13]. These brain adaptations could play an important role in delaying the onset of ADRD as greater CBF may prevent and/or reduce the accumulation of amyloid β in the brain, which is one of the main pathological hallmarks of AD [14]. Additionally, improved cerebral haemodynamics may help prevent or slow other conditions that act as risk factors for cognitive decline and ADRD, such as cardiovascular disease (CVD) and diabetes [15]. Although steady-state CBF normally declines with post-maturation ageing, chronic diseases like CVD, hypertension, and diabetes can accelerate age-related CBF alterations and lead to disruption of neuronal homeostasis [16, 17].

Existing scientific literature suggests that high levels of physical activity can positively impact cognitive function in middle-aged (50–64 years) and older (> 65 years) individuals [18–24]. Sofi and colleagues (2011) examined 15 prospective cohort studies that collectively followed more than 30,000 healthy older adults over 1–12 years. Individuals who were more physically active before the follow-up period had a 38% reduced risk of cognitive decline compared to those with a sedentary lifestyle at baseline [22]. Cross-sectional studies have found an association between higher levels of physical activity in older adults with both better performance on specific cognitive tasks [23, 25] and reduced risk of cognitive decline [24].

Evidence from neuroimaging studies also supports the positive effects of exercise on brain health. Exercise has been shown to reduce age-related atrophy in grey and white matter [26], decrease both brain [27] and hippocampal atrophy [28], and increase white matter integrity [29, 30]. Animal models suggest changes in neurotrophic factors in response to exercise may be partially mediated by enhanced levels of brain-derived neurotrophic factor (BDNF) and insulin-like growth factor (IGF-1) in the hippocampus [31]. BDNF improves overall neural health by increasing brain vascularization, neurogenesis, and synaptic efficiency in the hippocampus [31]. As BDNF plays a role in memory formation, enhanced levels of BDNF in the brain may help prevent memory loss and cognitive decline with ageing [31].

The literature on the associations between exercise, cognition, and brain health in older individuals primarily comprised epidemiological and observational studies [22–24, 29, 30]. These study designs only allow passive observation of events and are prone to selection, information, and confounding bias compared to RCTs and cannot be used to determine causality. The few RCTs investigating the relationship between exercise, cognition, and brain health have found, however, contradictory results [12, 32–34]. Possible explanations for the conflicting literature include sub-optimal study design and methods, such as small sample sizes, short exercise interventions, and inadequate tracking of participant adherence to prescribed exercise routines [8, 34, 35]. The methodological limitations of previous studies support the need for new well-designed RCTs to investigate the association between exercise and cognitive function in older adults [21].

Most prior RCTs of the effects of exercise did not include older participants at greater risk for ADRD due to CVD and/or genetic risk factors. Both CVD and ADRD share a number of risk factors (i.e., age, obesity, physical inactivity, smoking, elevated blood pressure, and high cholesterol) [36]. Older individuals with CVD risk factors may benefit more from exercise interventions in terms of their brain health and/or cognitive performance. People who have a family history of ADRD might also gain more from exercise programmes due to their genetic susceptibility from, for example, carrying the apolipoprotein E (*APOE*) e4 allele. Individuals with at least one *APOE* e4 allele copy are at greater risk of developing AD [37].

Given the estimates of the burden of ADRD and the promising evidence of the benefits of exercise on cognitive health, we propose an RCT of aerobic exercise for individuals at increased risk of ADRD. This RCT will test the efficacy of a 6-month aerobic exercise intervention for the primary and secondary prevention of ADRD in older adults (50–80 years old). We will measure the cognitive and cerebrovascular outcomes, including vascular reactivity, vascular biomarkers, and changes in the brain structure and function using magnetic resonance imaging (MRI). A unique feature of this study is the inclusion of assessments linking vascular risk factors, neuroimaging markers, sleep, genetic risk, and cognitive health outcomes. The primary aim of this study is to determine the independent effect of aerobic exercise on a cognitive composite score, calculated as the average of ten cognitive tests (executive functioning, complex attention, processing speed, and verbal memory), between participants allocated in the aerobic vs stretching-toning groups. We hypothesize that participants randomized to the 6-month aerobic exercise intervention will score higher in the cognitive composite score following 6 months of training compared to participants allocated to a stretching-toning exercise intervention (control group). The secondary aims are to examine the comparative effects of aerobic exercise and stretching-toning on a number of secondary outcomes noted in the text and whether exercise-related changes persist 12 months after completion of the exercise intervention (i.e., at 18 months) and if a telephone-based behavioural support intervention leads to improved maintenance of the exercise-related benefits. We hypothesize that the effects of improved aerobic fitness and brain health (e.g., increase in resting CBF) seen at 6 months with aerobic exercise will be at least partially maintained at the end of the follow-up period and that the telephone-based behavioural support intervention will be more effective in leading to persistent lifestyle changes and greater retention of any benefits that arise. To test these hypotheses, the participants will be randomly allocated into one of four treatment arms: (1) aerobic exercise and health behaviour support, (2) aerobic exercise and no health behaviour support, (3) stretching-toning and health behaviour support, and (4) stretching-toning and no health behaviour support.

## Methods

The Brain in Motion II Study is an 18-month randomized controlled trial (RCT). It is open labelled with blinded evaluation superiority (*aerobic exercise superior to stretching-toning*) trial of four-armed parallel groups with a 1:1:1:1 allocation ratio. The trial utilizes a PROBE (Prospective, Randomized, Open with Blinded End-points) design [38]. The study protocol has been approved by the University of Calgary Conjoint Health Research Ethics Board (REB16-1199) and registered with ClinicalTrials.gov (NCT03035851). The RCT will be carried out according to the CONSORT and SPIRIT guidelines.

### Participants

A total of 264 male and female participants at elevated risk of ADRD between the ages of 50 and 80 will be recruited from the community in Calgary, Alberta, Canada, and surrounding areas via printed advertisements (e.g., posters and newspaper ads), media campaigns, and from physician offices through the University of Calgary Department of Family Medicine Teaching Clinics.

### Eligibility criteria

A full listing of the inclusion and exclusion criteria is presented in Table 1. This study will include inactive men and women 50–80 years of age at baseline who have subjective cognitive symptoms but no dementia and either one or more CVD risk factors for ADRD or a family history of ADRD. The study exclusion criteria are as follows: age less than 50 or greater than 80 years, current physical activity greater than 150 min per week of moderate-to-vigorous intensity physical activity, absence of CVD risk factors, presence of dementia (based on DSM-5 criteria) or severe cognitive deficits (Modified Telephone Interview for Cognitive Status (TICS-M) score < 20), presence of a developmental handicap, terminal illness (life expectancy < 1 year), non-fluency in verbal and written English, history of stroke, current participation in another clinical trial, comorbid medical or neurological illnesses (e.g., multiple sclerosis) that would confound cognitive assessments or make trial completion unlikely, and contraindication for the aerobic or stretching-toning interventions.

**Table 1 Tab1:** Inclusion and exclusion criteria for the *Brain in Motion II* trial

Inclusion criteria	Exclusion criteria
• Men and women aged 50–80 years (inclusive) • Inactive (engagement < 150 min/week of moderate-to-vigorous exercise) • Subjective cognitive symptoms but no dementia^a^ • One or more CVD risk factors for ADRD or family history of ADRD^b^ • Female participants must be post-menopausal • Able to walk independently outside, as well as up and down the stairs of 20 steps	• Presence of dementia (based on the DSM-5 criteria) or severe cognitive deficits (TICS-M score < 20)^a^ • Absence of CVD risk factors or family history of ADRD^b^ • Diagnosis of severe asthma or COPD (respiratory) • Presence of a developmental handicap • Terminal illness (life expectancy < 1 year) • Not fluent in verbal and written English • History of stroke or serious cardiovascular condition • Current participating in another trial • Comorbid medical or neurological illness that would confound cognitive assessments or make trial completion and unlikely^c^ • Contraindication for exercise interventions

^a^Existing or suspected dementia will be identified by medical history, cognitive impairment on the Telephone Interview for Cognitive Status (TICS-modified; score ≤ 20), or impaired Instrumental Activities of Daily Living (IADL)—a response of needs assistance or dependent due to cognitive impairments on any item on the Lawton scale

^b^Cardiovascular disease (CVD) risk factors for Alzheimer’s disease and related dementias (ADRD) include the history of hypertension, diabetes mellitus, obesity (body mass index (BMI) BMI ≥ 30 but < 40 kg/m^2^), elevated cholesterol, current smoking, and history of coronary artery disease without recent (< 5 years) symptoms. Family history of ADRD is defined as having a first-degree relative (parent, sibling, or child) who has been diagnosed with ADRD

^c^E.g., persistent post-concussive symptoms or medication for psychological condition that would impact cognitive performance

Inactivity will be assessed with a physical activity questionnaire [39] and defined as an engagement in < 150 min/week of moderate-to-vigorous exercise [40]. The subjective cognitive symptoms, family history of dementia, CVD risk factors for ADRD, family history of ADRD, and current physical activity level will be assessed during a telephone interview. The aim is to recruit participants with either subjective cognitive decline or mild cognitive impairment who are at risk for progressive cognitive decline and dementia. This recruitment strategy is similar to the one used in a previous RCT that showed that exercise reduced the likelihood of cognitive decline [41], as measured by the Clinical Dementia Rating Scale [42]. That scale has been validated [43] and allows, with reasonable accuracy, the identification of individuals with mild cognitive impairment and those with very early AD. The presence of suspected dementia will be identified by medical history and cognitive impairment on the Telephone Interview for Cognitive Status (TICS-modified; score ≤ 20 [44, 45];). The CVD risk factors for ADRD include a history of hypertension, diabetes mellitus, obesity (body mass index (BMI) < 40 kg/m^2^), elevated cholesterol, current smoking, and coronary artery disease without recent (< 5 years) symptoms. A family history of ADRD is defined as having a first-degree relative (parent, sibling, or child) who has been diagnosed with ADRD.

Following the telephone evaluation, the participants will be provided with a copy of the informed consent form to review—prior to the first one-site visit—as part of a “welcome package” and will also be asked to provide written permission to contact their family physician for medical clearance to participate in the study. The study coordinator will be responsible for obtaining the informed consent. Participants will then attend a 60-min on-site clinical laboratory eligibility screening session in which a written informed consent will be obtained by the study coordinator. During this visit, the participants will also complete the following assessments: the Brain Injury Screening Questionnaire (BISQ [46];), the Montreal Cognitive Assessment (MoCA [47];, the Memory Assessment Clinic questionnaire (MAC-Q [48];), and the Physical Activity Readiness Questionnaire (PAR-Q+ [49, 50];). The BISQ is a screening tool used to identify a lifetime history of traumatic brain injury [46]. The MoCA score will be used to stratify the participants at baseline prior to their allocation into different experimental groups (see below). The MAC-Q is a validated measure of subjective memory complaints that has been previously used in healthy older and clinical/research populations [51]. Finally, the PAR-Q+ form will be used to determine the safety of exercise programme participation. This form will be completed by the participants and included in a fax sent to the participant’s family physician requesting medical clearance to participate in the study. A certified exercise physiologist will review this questionnaire with participants prior to completing their exercise testing. Additionally, participants will be requested to complete a sociodemographic questionnaire and report on their use of medications and other therapies.

### Risks

Risks of exercise include falls, musculoskeletal injuries, coronary heart disease events (myocardial infarct, acute coronary syndrome), and other side effects that are generally minor. Our previous experience with similar exercise interventions gives our team considerable expertise on the means to mitigate these types of health risks. Maximal cardiopulmonary testing will be conducted by certified exercise physiologists with a physician on-call and present for high-risk participants and appropriate emergency equipment available. A participant may be withdrawn from the study if a research procedure is judged to be potentially harmful or presents an unacceptable risk of injury to the participant. For example, participants could be withdrawn if they develop an abnormality (e.g., abnormal ECG suggesting an unstable cardiac issue, uncontrolled hypertension) that is judged by a physician associated with the study or the participant’s attending physician to pose a risk to the participant if they continue in the study.

### Sample size

Preliminary estimates of the effect sizes for improvement in overall cognition (cognitive composite score) with aerobic exercise training are based on the results of a previous study from our group, the Brain in Motion Study [52], that used similar active intervention and outcome. This study will recruit a total of 264 participants. This power calculation, which is based on a sample size calculation formula for a mixed model for repeated measures data with attrition [53], provides 80% power to detect 0.4 standard deviation between-group difference for an average repeated measurement correlation of 0.6 and three repeated measurements, taking 20% attrition into consideration (based on the *Brain in Motion* Study [52];).

### Randomization

This study will be a prospective open label with blinded evaluation (PROBE) trial and randomize the participants into one of the following four treatment arms:
Aerobic exercise and health behaviour support: Participants will undergo aerobic exercise training for 6 months and will receive 1-year of individually tailored telephone support after the intervention.Aerobic exercise and no health behaviour support: Participants will undergo aerobic exercise training for 6 months and will not receive health behaviour support during the follow-up 1-year follow-up period (at 18 months).Stretching-toning and health behaviour support: Participants will undergo stretching-toning exercise training and will receive 1-year of individually tailored telephone support after the intervention.Stretching-toning and no health behaviour support: Participants will undergo stretching-toning exercise training and will not receive health behaviour support during the follow-up 1-year follow-up period (at 18 months).

Randomization sequence within blocks will be generated by computer using a random number generator. Randomization will be stratified by age (age > 65 vs ≤ 65 years) and sex with blocked, simple randomization into each of 4 strata for each group of participants as they enter the study. Because enrolment occurs in complete groups of participants (rather than sequentially), randomization will be done in complete blocks such that randomness of allocation is completely preserved. Specifically, recruitment for each study site (e.g., University of Calgary, YMCA Calgary) will be done independently. Once the desired number of participants (8–15 participants) are recruited, baseline testing will be conducted. Participants will be then randomized (the random sequence will be generated by computer: REDCap randomization tool) and immediately start the exercise intervention. Randomized allocation will be completely masked to all study personnel, except the database programmer (study coordinator) who will not participate in any participant or protocol-related activities. Participants will receive a “welcome package” containing their allocation group during the baseline testing visits, in advance of the exercise programme starting date.

### Blinding

The nature of both the aerobic exercise intervention and health behaviour intervention precludes participants from being blinded to the group status; however, the researchers assessing any of the outcome variables will be blinded to participant group assignment to avoid bias in result interpretation. Since patients are not blinded, safety can be assessed in the context of the actual intervention, and, therefore, the research team will remain blinded to the group allocation.

### Study design

Figure 1 displays an overview of the study design and participant flow through the trial. Once a participant is eligible to join the study, he or she will be asked to provide additional information during the 60-min on-site eligibility screening session, including basic socio-demographic information (e.g., sex and gender), medical history (cardiovascular, respiratory, neurological), lifestyle habits (e.g., smoking history, physical activity levels), descriptive physical data (e.g., height, weight), level of education, current and past income and occupation, and current medications (prescribed, over-the-counter, and vitamins or supplements).

**Fig. 1 Fig1:**
[figure not shown]
Overview of study design and participant flow through the trial

After the completion of the screening procedures, the participants will be randomly assigned to one of the four experimental groups. Following randomization, participants will undergo their first set of cerebrovascular/physiological, neuroimaging, sleep, and cognitive factors and will complete several lifestyle and psychological questionnaires (see Table 2). This battery of assessments will be completed again following the 6-month intervention period and after a 1-year follow-up period.

**Table 2 Tab2:** Schedule of physiological, cognitive, psychological, and neuroimaging assessments for the *Brain in Motion II* trial

Assessment measure	Screening assessments	Visit (months)			
		0	3	6	18

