### Statistical analyses

The primary outcome analysis will use mixed-effects regression analysis to assess the effects of exercise on a composite cognitive score where the aerobic exercise intervention group will be compared to the stretching-toning group while adjusting for the participants’ baseline characteristics (age, sex, MoCA score, years of education, and baseline physical fitness level). The adjusted estimates of the mean change in cognitive composite score for each group will be reported along with the corresponding 95% confidence intervals. Statistical significance will be set at *P* < 0.05, and all tests will be two-sided. The assessment of effect modification (heterogeneity of treatment effect) will be performed with the inclusion of multiplicative interaction terms for age, sex, APOE status, CBF, V̇O_2_max, and sleep quality. A final analysis plan, which includes analyses of the secondary outcomes and strategies for handling missing/incomplete data, will be formalized by the investigators prior to breaking the blind. The data analysis will only begin once data collection is complete.

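### The protocol gives two incompatible orders for month-0 testing and randomization, and has the arm disclosed within the baseline visits, so baseline values may be measured after allocation is known

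*Protocol article*

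**What the plan says.** Three statements in the protocol article fix the timing.

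- **Randomization section, sequence of steps.** "Once the desired number of participants (8–15 participants) are recruited, baseline testing will be conducted". The next sentence continues: "Participants will be then randomized (the random sequence will be generated by computer: REDCap randomization tool) and immediately start the exercise intervention". Testing comes first, allocation second, and exercise follows at once.
- **Randomization section, disclosure.** Participants are given a package "containing their allocation group during the baseline testing visits, in advance of the exercise programme starting date".
- **Study design section, text under Fig. 1.** "After the completion of the screening procedures, the participants will be randomly assigned to one of the four experimental groups". It goes on: "Following randomization, participants will undergo their first set of cerebrovascular/physiological, neuroimaging, sleep, and cognitive factors". Allocation comes first, testing second.

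The Blinding section says that participants cannot be blinded, while outcome assessors are. The Primary outcome section has the composite measured at baseline, 6 and 18 months. The Statistical analyses section reports the adjusted mean change in the composite by group, and adjusts for "baseline characteristics (age, sex, MoCA score, years of education, and baseline physical fitness level").

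**The concern.** A baseline value is protected by randomization only if allocation cannot have influenced it. The neuropsychological battery and the maximal treadmill test depend on effort, and the questionnaires are self-reported. A participant who already knows whether he or she will do aerobic exercise or stretching-toning may try harder, try less, or answer differently. The month-0 composite is the starting point for the reported change, and baseline fitness is a covariate in the primary model. If either is collected after the arm is known, a difference between arms at month 0 may be a consequence of allocation and not chance, and the comparison of change carries that difference with it. Data collected this way cannot be repaired later, so the order has to be unambiguous in the protocol.

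**Working it through.** The point rests on the order of procedures. The documents give no figure to reproduce, so the check is a comparison of the texts followed by a short piece of algebra.

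1. **Is the first set of assessments the month-0 battery?** Yes. The Study design section adds: "This battery of assessments will be completed again following the 6-month intervention period and after a 1-year follow-up period". Table 2 lists the neuropsychological battery and the maximal aerobic capacity test at months 0, 6 and 18 and not at screening. The set tested after randomization in that section is therefore the same as the baseline testing in the Randomization section.

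2. **Can both orders hold?** No. One places this battery before allocation, the other after it. Fig. 1 is not available here, but no figure could make both sentences true.

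3. **Is the Randomization section consistent with itself?** Not comfortably. If allocation is generated only once baseline testing is done, and exercise then starts immediately, there is no allocation to hand over during the baseline visits. The welcome package described under Eligibility criteria does not explain this: it carries the consent form and is sent before the first on-site visit.

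4. **Which analysis inputs are exposed?** The month-0 composite and baseline fitness. The article does not define the fitness covariate; I assume that it comes from the month-0 treadmill test, the only fitness test in Table 2. Age, sex and education do not depend on when testing takes place, and MoCA is a screening measure in Table 2. These four covariates are unaffected.

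5. **How would the exposure enter the estimate?** Let τ be the true effect on the composite at 6 months. Let δ₀ and δ₆ be the between-arm shifts (aerobic minus stretching-toning) that knowledge of the arm produces at months 0 and 6.
   - Month-0 testing before disclosure: change contrast = τ + δ₆.
   - Month-0 testing after disclosure: change contrast = τ + δ₆ − δ₀.
   - The order of testing therefore contributes −δ₀. If disappointed stretching-toning participants do worse at month 0, δ₀ is positive and the estimate is biased against aerobic exercise. If they try harder, the sign reverses. If the shift is the same at both visits, the two terms cancel.
   - If knowledge of the arm shifts measured fitness by φ between arms, and fitness enters the contrast with coefficient γ, adjustment adds −γφ.

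6. **Can these terms be given values?** No. The documents contain no information on δ₀, δ₆, φ or γ. The correlation of 0.6 in the Sample size section is between repeated measurements of the outcome. It could scale δ₀ only if the baseline composite were a covariate, and it is not in the list of covariates. It does not describe the link between fitness and cognition.

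**The case against.** The other side has a good case on several points.

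- **A reader might infer that participants certainly know their arm when tested.** The documents do not say so. The Study design section concerns when allocation happens, not when it is revealed, and the Randomization section masks allocation from nearly all staff. Only the package sentence speaks of disclosure. It refers to visits in the plural, so handing over the package at the end of the last visit would satisfy it. This stands: testing with knowledge of the arm is possible under the text, not stated by it.
- **The Randomization section is the more operational text and gives the sound order.** The sentence under Fig. 1 may be a loose summary. That is plausible, but the disclosure sentence sits in the operational section and agrees better with the other order, so a slip of wording cannot be assumed.
- **Assessors are blinded, and the Discussion cites a survey in which respondents expected similar cognitive results from aerobic and non-aerobic training.** Both reduce the concern. Neither removes it: blinded assessors do not control a participant's effort, and the survey as described concerned expected cognitive performance, not effort on a treadmill test or self-report.
- **A reader might also infer a loss of analysable participants, or harm from early knowledge of the telephone-support arm.** Neither is needed here. Those who withdraw are invited to follow-up assessments, and handling of missing data is left to the final analysis plan. Support is crossed 1:1 with exercise, so it is balanced across the primary contrast; withholding that part of the allocation until month 6 would be a design preference, not the correction of an error.

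**Conclusion.** The protocol is wrong as written: an internal inconsistency. The two sections cannot both describe the order of month-0 testing and randomization, and the disclosure sentence does not fit the order given in its own section. The consequence is conditional. If the Study design order and the disclosure sentence are both followed in an open-label trial, the month-0 composite and the fitness covariate may be measured after participants know their arm, and the primary comparison could be biased.

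A percentage of the 0.4 SD target effect would be tempting, but any such figure would only rescale an assumed shift. Neither size nor direction can be derived from the documents. The conclusion assumes that the sentences mean what they say and that baseline fitness is the month-0 treadmill result; the contradiction itself needs neither an assumed shift nor that second reading.

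**What to change.** **Wording.** Rewrite the Study design text under Fig. 1 and the package sentence in the Randomization section to one order: all month-0 assessments in Table 2 are completed, then the allocation is generated, and participants are told only after their last baseline visit. Check that Fig. 1 shows the same order.

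**Participants already enrolled.** Enrolment began in January 2017, so new wording cannot change month-0 data already collected. Use the dates of testing, randomization and disclosure to report, by arm, how many were tested after disclosure, and run a sensitivity analysis of the primary outcome that excludes them. The article does not say whether the date of disclosure is recorded. Where it is missing, say so and treat the order for that participant as unknown.

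**Cost.** A text amendment, a rule on when the allocation is released, and a short gap between the last baseline visit and the first class. The Trial status section says that new enrolment was on hold at submission, so the rule can be in place before recruitment resumes.
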